### Sample Size Calculation

A preliminary survey was conducted among 20 patients admitted to the Department of Rheumatology and Clinical Immunology at our hospital between January 2020 and August 2022. The proportion of patients who were unable to complete treatment with hematological toxicities was 65% (13/20). None of the patients failed to complete the treatment because of nonhematological adverse events. The proportion of patients who could not complete treatment for reasons other than adverse events was 5% (1/20). Except for the above cases, none of the other patients failed to become CMV pp65–negative within 3 weeks. Approximately 30% of the patients achieved CMV pp65 negativity within 3 weeks without severe hematologic adverse events. The incidence of hematologic toxicities when GCV AUC was maintained at 40-60 μg·h/mL by TDM was estimated to be 36.5%, based on a previous report [9]. Assuming that the rate of treatment incompletion due to reasons other than adverse events or the rate of failure to achieve CMV pp65 negativity within 3 weeks remained at 5%, the estimated rate of patients who would fail to complete treatment owing to adverse events or fail to achieve CMV pp65 negativity within 3 weeks of TDM would be 41.5%. Therefore, the proportion of patients expected to achieve CMV pp65 negativity within 3 weeks without adverse events under TDM was assumed to be 58.5%. Under conditions of a 2-sided significance level of 5% and a power of 80%, the required sample size to detect an increase in the proportion of patients completing treatment without adverse events was determined to be 31. Considering potential dropouts, the sample size was set at 40.

### Ethical Considerations

This study was approved by the Clinical Research Ethics Committee of Kobe University (C230016) on June 28, 2024. This trial was registered in Japan Registry of Clinical Trials (jRCTs051240080) on June 28, 2024. All the participants will sign an informed consent form after receiving a detailed explanation of the study from the researchers. All participant data will be deidentified prior to analysis. Participants will not receive any financial compensation for their participation. This study will adhere to the protocols and principles outlined in the Declaration of Helsinki. Any modifications to the protocol will require approval from the ethics committee before implementation. To address potential claims resulting from health issues related to the study, the principal investigator has secured clinical research insurance covering compensation for death, serious disability, medical expenses, and medical benefits.

### Outcomes

#### Primary End Point

The primary end point of this study is to determine whether preemptive therapy with VGCV for CMV reactivation could achieve CMV antigenemia negativity within 3 weeks without severe adverse events. Severe adverse events are defined as leukopenia, neutropenia, anemia, and thrombocytopenia classified as grade 3 or higher according to the Common Terminology Criteria for Adverse Events (CTCAE) version 5.0.

#### Secondary End Points

Secondary end points include the change in CMV antigen levels at weekly intervals after VGCV initiation, the total dose of VGCV administered, and the duration of preemptive therapy. Additionally, this study will examine the occurrence, type, and severity of adverse events caused by VGCV for a safety assessment. Furthermore, data that would be relevant to the efficacy or safety of preemptive therapy (estimated AUC at each time point of TDM measurement, Ccr at each time point of TDM measurement, CMV pp65 negativity within 3 weeks of VGCV administration, GCV plasma concentration at each measurement point, total GCV exposure, VGCV dose based on renal function at registration, and CMV antigen repositivity within 2 weeks of completion of treatment), pharmacokinetic parameters of GCV, blood concentration of GCV obtained from DBS, genetic polymorphisms of *NUDT15*, and CMV-PCR value will be collected.

### Statistical Analysis

All analyses will be conducted using R software (version 4.5.1; R Foundation for Statistical Computing).

#### Primary Analysis

A binomial test will be performed for the primary end point. The null hypothesis will be defined as 30% of patients having completed preemptive therapy without severe adverse events. The *P* value will be used as the reference.

#### Secondary Analysis

The number of CMV pp65–positive cells will be examined before and weekly after the initiation of preemptive therapy, and the absolute and relative reductions in the number of these cells compared to baseline will be calculated. Correlation analyses between the absolute or relative reduction in the number of CMV pp65-positive cells and the estimated AUC will also be determined. Further, the median (or mean) total dose of VGCV and the duration of administration will be calculated. The types, severity, and incidence rate of adverse events during the study period will be summarized and stratified by renal function (Ccr≤30, 30<Ccr ≤60, 60<Ccr≤80, Ccr>80 mL/min) or estimated AUC (AUC<40, 40≤AUC≤60, AUC>60 μg·h/mL). Group comparisons will be conducted using Fisher exact test or other appropriate statistical methods.

#### Exploratory Analysis

The median (or mean) of the estimated AUC and dose-adjusted estimated AUC will be calculated for each renal function at the start of treatment (Ccr≤30, 30<Ccr≤60, 60<Ccr≤80, Ccr>80 mL/min). Kruskal-Wallis and Dunn multiple comparisons tests will be performed for each group. A correlation analysis will be conducted between Ccr and the recommended probable dose by using Bayesian estimation. Single and multiple regression analyses with the dose-adjusted estimated AUC as the objective variable and clinical information as the explanatory variables will be performed to explore the factors affecting the dose-adjusted estimated AUC. The proportion of CMV antigen-positive cells that disappear in less than 3 weeks of treatment will be calculated, and a binomial test will be performed against the proportions in the preliminary study. The patients will be grouped according to the presence or absence of disease or CMV infection recurrence, and the median (or mean) of the estimated trough blood concentration, estimated AUC, and total exposure will be calculated in each group. If necessary, the Mann-Whitney *U* test will be performed. The actual total dose of VGCV during the preemptive therapy and the total dose assuming that VGCV is administered at the dose stated in the package insert will be calculated, and a Wilcoxon signed-rank test will be performed. Patients will be grouped according to *NUDT15* genotype (wild-type, homozygous variant or heterozygous variant), and the number and proportion of adverse events in each group will be calculated. Fisher exact test will be performed. Additionally, the median (or mean) estimated trough plasma concentration, estimated AUC, and total exposure will be calculated for each group, and a Mann-Whitney *U* test will be conducted. If both CMV pp65 antigen and CMV-PCR are positive, the correlation will be analyzed using the Spearman rank correlation coefficient. *P* values calculated from the above analyses will be used as references.

Correlation analysis will be performed between plasma obtained by regular venous blood sampling and whole blood concentrations obtained via DBS. A preliminary analysis will be performed in 20 cases, which is half the sample size. If no clear correlation is determined, blood sampling using the DBS method will be discontinued in subsequent studies. Additionally, a simple regression analysis will be conducted with DBS whole blood concentration as the dependent variable and conventional plasma concentration measurements and clinical information as the independent variables.

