### Intervention

The study schedule is presented in Table 1. Patients will receive VGCV orally at the dosage specified in the package insert, based on creatinine clearance (Ccr) calculated using the Cockcroft-Gault equation [15]. On day 3 following the initiation of VGCV therapy, venous blood samples will be collected before and 2 hours after the morning dose of VGCV. The plasma concentrations will be measured using liquid chromatography-tandem mass spectrometry [16].

**Table 1 table1:** Summary of the study schedule.

		Hospitalization	Preobservation period	Treatment period									Closeout		Postobservation period
				Week 1					Weeks 2-3						
				Day 1	Day 3	Day 4	Day 5	Day 1		Day 2	Day 3				

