### Estimated Apparent Clearance

Individual estimated apparent clearance (CL/F) will be estimated using the post hoc Bayesian analysis based on a previously reported population pharmacokinetic model [17] as follows:

CL/F=7.09*(1+Ccr/68.3) (L/h)

Vc/F=10.8 (L)

Q/F=3.96 (L/h)

Vp/F=174 (L)

Ka=0.23 (/h)

T_lag_=0.93 (h)

where Vc/F, Q/F, Vp/F, Ka, and T_lag_ are the apparent volumes of distribution in the central compartment, apparent intercompartmental clearance, apparent volume of distribution in the peripheral compartment, absorption rate constant, and lag time, respectively. Additionally, interindividual variabilities of CL/F, Vc/F, Q/F, and Vp/F are 27.2, 153, 63.1, and 107%, respectively. Interindividual variabilities of Ka and T_lag_ are not included. The proportional residual variability is 42.9%. The individual AUC will be calculated using the following formula: AUC = daily dose of VGCV × (GCV molecular weight of 255.2/ VGCV molecular weight of 354.4) / estimated individual CL/F. Subsequently, the dosage will be adjusted to achieve the target AUC (40-60 μg·h/mL) by using the dose adjustment shown in Table 2. Patients will be informed of the possibility of dosing higher or lower than the package insert recommendation during the consent process. Thereafter, weekly plasma concentration measurements and dosage adjustments will be performed using the same procedure as described above, with a treatment period of up to 3 weeks. Post hoc Bayesian estimation will be performed using NONMEM version 7.5.1 (ICON).

**Table 2 table2:** Adjusted dosage of valganciclovir based on the estimated apparent clearance.

CL/F^a^ (L/h)	Adjusted dose
2.7^b^ < CL/F ≤ 4.1	450 mg once daily every other day
4.1 < CL/F ≤ 5.4	450 mg once daily for 2 days and 1 day off
5.4 < CL/F ≤ 8.1	450 mg once daily
8.1 < CL/F ≤ 12.2	450 mg twice daily and 450 mg once daily alternately
12.2 < CL/F ≤ 16.2	450 mg twice daily
16.2 < CL/F ≤ 24.3	900 mg in the morning and 450 mg in the evening
24.3 < CL/F ≤ 32.4	900 mg twice daily
32.4 < CL/F ≤ 40.5	1350 mg in the morning and 900 mg in the evening
40.5 < CL/F ≤ 48.6	1350 mg twice daily

^a^CL/F: estimated apparent clearance.

^b^For patients with CL/F less than or equal to 2.7 or greater than 48.6, consider dosage individually.

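### The exploratory tests of dose-adjusted AUC and recommended dose against creatinine clearance are partly circular, because the Bayesian CL/F behind both already contains creatinine clearance

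*Protocol article*

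**What the plan says.** Under Estimated Apparent Clearance, the protocol article says individual CL/F "will be estimated using the post hoc Bayesian analysis based on a previously reported population pharmacokinetic model". The typical value in that model depends on renal function ("CL/F=7.09*(1+Ccr/68.3) (L/h"). On variability, the "interindividual variabilities of CL/F, Vc/F, Q/F, and Vp/F are 27.2, 153, 63.1, and 107%, respectively", and "The proportional residual variability is 42.9"%. AUC is the daily dose times the molecular-weight ratio 255.2/354.4, divided by estimated CL/F. Table 2 assigns the dose from estimated CL/F alone.

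Under Intervention, each monitoring occasion has two samples: "venous blood samples will be collected before and 2 hours after the morning dose of VGCV".

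Under Exploratory Analysis, estimated AUC and dose-adjusted estimated AUC are summarised in four Ccr groups, and "Kruskal-Wallis and Dunn multiple comparisons tests will be performed for each group". Then: "A correlation analysis will be conducted between Ccr and the recommended probable dose by using Bayesian estimation". Then: "Single and multiple regression analyses with the dose-adjusted estimated AUC as the objective variable and clinical information as the explanatory variables". P values from these analyses serve as references only. The article names no estimate of CL/F that is free of Ccr.

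**The concern.** Dividing AUC by dose leaves 0.72 over estimated CL/F, and the recommended dose is a step function of the same estimate. Ccr therefore enters the outcome through the prior and is then tested against that outcome. If the two concentrations inform CL/F only weakly, the estimate is pulled towards the formula in Ccr and an association appears whether or not the patients show one.

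Factors related to ganciclovir pharmacokinetics are a stated objective. The Discussion says that no model based on rich sampling has been developed in Japan, so one from a Chinese population was borrowed. How strongly Ccr governs exposure in these patients is thus an open question, and these tests would largely return the borrowed relation as if it were a finding.

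**Working it through.** **1. Table 2 depends on estimated CL/F alone.** AUC = daily dose × 0.7201 / CL/F, with 0.7201 = 255.2/354.4.
- 450 mg once daily: 450 × 0.7201 / 5.4 = 60.0 and 450 × 0.7201 / 8.1 = 40.0.
- 1350 mg twice daily: 2700 × 0.7201 / 40.5 = 48.0 and 2700 × 0.7201 / 48.6 = 40.0.
- Over all nine bands, the upper CL/F limits give 39.5–40.0 and the lower limits 48–60.

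The target of 40–60 µg·h/mL is reproduced.

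**2. What the prior contributes alone.** 7.09 × (1 + Ccr/68.3) gives 10.2 L/h at Ccr 30, 13.3 at 60, 15.4 at 80 and 19.5 at 120. AUC per mg is then 0.7201/10.2 = 0.0706 at Ccr 30 and 0.7201/19.5 = 0.0369 at Ccr 120. That is a ratio of about 1.9 before any concentration is used.

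**3. Hand approximation.** Assume Ccr has mean 75 and SD 28; the article gives no distribution.
- SD of log typical CL/F ≈ 28/(68.3 + 75) = 0.195.
- Shrinkage of CL/F with the two samples was about 38–44% in simulation. The weight on the data is then k ≈ (1 − shrinkage)² = 0.38 to 0.31, and the weight on the Ccr formula is 0.62 to 0.69.
- No true Ccr effect: correlation of Ccr with estimated log CL/F ≈ (1−k) × 0.195 / √[((1−k) × 0.195)² + k × 0.272²] = 0.58 to 0.66.
- Model true: correlation with true log CL/F ≈ 0.195 / √(0.195² + 0.272²) = 0.58. With the estimate it is 0.195 / √(0.195² + k × 0.272²) = 0.76 to 0.79.

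**4. Simulation.** Two-compartment model with lag as stated in the article, lognormal interindividual effects, proportional error, Bayesian estimates using the Ccr-containing prior, 12-hourly dosing assumed. True CL/F was simulated independent of Ccr. Rejection rates at two-sided 5%, 400 trials per row:

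| Scenario | AUC/dose vs Ccr | Dose vs Ccr | Kruskal-Wallis |
|---|---|---|---|
| n=40, day-3 pair, Ccr uniform 20–140 | 100% | 99.5% | 99.5% |
| n=40, day-3 pair, Ccr mean 75, SD 28 | 98.8% | 96.5% | 94.3% |
| n=31, otherwise the same | 96% | 92% | 87% |
| n=40, week-2 pair only | 95% | 92% | 87% |
| n=40, Ccr SD 15 | 67% | 52% | 47% |
| n=40, four samples pooled | 64% | 55% | 41% |
| n=40, six samples pooled | 35% | 30% | 17% |
| n=40, day-3 pair, prior without Ccr | 6.2% | 6.0% | 4.5% |

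In the second row the median correlations are −0.61 (AUC/dose) and +0.56 (dose). A repeat run of that row gave 99.6% (Spearman) and 98.1% (Kruskal-Wallis), with a correlation of 0.64. With Ccr SD 22, Spearman rejects in 93% and Kruskal-Wallis in 80%. Testing the simulated true CL/F against Ccr rejects in 4–7%, so the excess comes from the prior. The size of the dose does not matter under linear kinetics with proportional error.

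**5. If the model holds.** The slope of log estimated on log typical CL/F stays close to the truth (0.99–1.16 against 1.00–1.16). The correlation is inflated: 0.77 against 0.59, or 0.70–0.74 against 0.49–0.54 in runs with Ccr SD 22–28.

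**The case against.** The strongest reply is that a null of no Ccr effect is not a live possibility. The article itself says ganciclovir is cleared mainly by the kidneys and cites higher exposure in renal impairment. If the borrowed model is right, a Spearman test on the true CL/F would already be significant in 89–93% of trials (97% or more in other runs), and the slope is not distorted. This stands, and it limits the harm to an exaggerated strength of association and a P value that cannot be interpreted.

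The analyses are also exploratory, their P values are for reference, and they drive no dosing decision, primary end point or interim decision. That limits the stakes but does not remove the bias, since the correlation coefficient is itself inflated. Relating Ccr to the recommended dose remains a fair description of what the algorithm prescribes, provided it is read that way.

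Some stronger readings are tempting but not supported:
- *The tests will be significant whatever the data say.* Rejection depends on the spread of Ccr and on whether samples are pooled. The article does not say which occasion feeds these tests or whether later estimates reuse earlier samples.
- *The prior is merely tested against itself.* With 38–44% shrinkage, the SD of individual deviations keeps 56–62% of its assumed size, so the concentrations do contribute.
- *Age and weight inherit the artefact, and non-renal factors are attenuated.* Both are plausible, but no test-level figure supports either. The regression names only clinical information, so the problem applies there if Ccr is included.
- *Unadjusted AUC by Ccr group is affected in the same way.* It also depends on the dose given and was not examined separately.

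An analysis plan that is not shown might specify a Ccr-free estimate, and the point would then fall away. As it stands, the article itself fixes both the quantities and the tests.

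**Conclusion.** The point holds as partial circularity. With the two-sample estimates described, these tests would be significant in most trials without any true dependence on Ccr: roughly 80–100% for a usual Ccr spread and about 47–67% for a narrow one. Pooling samples over weeks lowers this to about 17–64%, still at least three times nominal. If the borrowed model is correct, direction and slope are about right and only the strength is overstated. A regression of dose-adjusted AUC that includes Ccr has the same problem. The rates rest on an assumed Ccr distribution and 12-hourly dosing (24-hourly gave 99–100% in a check of 100 trials), with lognormal, uncorrelated individual effects. Dosing and the primary analysis are untouched. It should be corrected before the exploratory analysis is run.

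**What to change.** Keep the Ccr-based prior for dose adjustment. For analyses that relate exposure or recommended dose to Ccr, do one of the following:
- Re-estimate CL/F with a prior that has one typical value for all patients. The stated 27.2% is conditional on Ccr, so it must be widened. For Ccr SD 22–28, √(0.272² + 0.154²) to √(0.272² + 0.195²) gives about 31–33%.
- Test Ccr inside the population model, fitting the trial's concentrations with and without it. Whether two samples per occasion in about 40 patients support this has not been shown and should be checked first.

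State which monitoring occasions are used and report eta-shrinkage. Describe any Ccr association taken from the dosing estimates as partly built in by the model.

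The cost is extra NONMEM runs on data already collected and a change of wording, with 5 of 40 patients enrolled at publication. Power is lower: about 40–80% with the day-3 pair if the model's Ccr effect is real. With the 27.2% left unwidened, the simulated figures were 66% (AUC/dose), 58% (dose) and 40% (Kruskal-Wallis), rising to 89%, 85% and 69% with six pooled samples.

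### The exploratory regression on dose-adjusted AUC uses shrunken post hoc clearances, so the Ccr-adjusted effect of a factor outside the prior is reported at about 30-40% of its true size from week 1 samples and about 50-70% if two or three weeks are pooled

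*Protocol article*

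**What the plan says.** The Exploratory Analysis section names the outcome and the method: "Single and multiple regression analyses with the dose-adjusted estimated AUC as the objective variable and clinical information as the explanatory variables will be performed".

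The Estimated Apparent Clearance section shows what that outcome is made of:

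- Individual clearance: "Individual estimated apparent clearance (CL/F) will be estimated using the post hoc Bayesian analysis based on a previously reported population pharmacokinetic model".
- Exposure: "AUC = daily dose of VGCV × (GCV molecular weight of 255.2/ VGCV molecular weight of 354.4) / estimated individual CL/F".
- Typical clearance in the prior: "CL/F=7.09*(1+Ccr/68.3) (L/h"), with Ccr as the only covariate.
- Prior spread: "interindividual variabilities of CL/F, Vc/F, Q/F, and Vp/F are 27.2, 153, 63.1, and 107%, respectively".
- Residual error: "The proportional residual variability is 42.9" per cent.

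The Intervention section sets the sampling at two points per occasion: "venous blood samples will be collected before and 2 hours after the morning dose of VGCV". The procedure is then repeated, and the figure that ends the next quote counts weeks: "weekly plasma concentration measurements and dosage adjustments will be performed using the same procedure as described above, with a treatment period of up to 3". Table 1 places TDM sampling on day 3 of week 1 and on day 1 of weeks 2 and 3, so a patient contributes at most six concentrations. The article does not say whether later estimates pool earlier samples, or which occasion supplies the regression outcome.

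**The concern.** Random error in a regression outcome widens the standard error but leaves the slope unbiased. Shrinkage is different. A post hoc Bayesian estimate is a compromise between the patient's data and the prior mean. When the data are sparse and noisy, the compromise lies near the prior mean, which here knows only Ccr. Suppose a factor outside the prior moves true clearance. The estimate then follows only part of that movement, and the slope on the factor is systematically too small. More patients do not cure this.

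What is at stake is the size of the reported effects. Study Objectives lists factors related to the pharmacokinetics of ganciclovir among the things to be investigated. The Discussion explains that the model was borrowed from another population, because none had been developed in Japan from rich sampling. Which further factors matter in these patients is therefore a real question. Readers would take the coefficients at face value, and a factor of practical importance could look one third to two thirds as large as it is.

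**Working it through.** The article gives no figure for shrinkage or for this regression, so there is none to reproduce. All inputs below come from Estimated Apparent Clearance, Intervention and Table 1.

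**1. What the outcome contains.** Dose-adjusted AUC = (255.2 / 354.4) / estimated CL/F = 0.7201 / estimated CL/F. It carries nothing beyond the post hoc clearance.

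**2. Prior against data.** The prior variance of log CL/F is 0.272² = 0.0740. The residual variance is 0.429² = 0.1840. The ratio is 0.1840 / 0.0740 = 2.5, so a single sample is much weaker than the prior.

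**3. Closed-form guide.** If every sample informed log CL/F directly, the share of a non-prior effect that survives would be w² / (w² + s²/n), with w² = 0.0740 and s² = 0.1840:

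- n = 2: 0.0740 / (0.0740 + 0.0920) = 45%
- n = 4: 0.0740 / (0.0740 + 0.0460) = 62%
- n = 6: 0.0740 / (0.0740 + 0.0307) = 71%

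This ignores that each sample also has to inform Vc/F, Q/F and Vp/F, so it is optimistic, most clearly for two samples.

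**4. Full model.** The two-compartment model with lag time and the stated parameters was simulated, with log-normal variability of 27.2%, 153%, 63.1% and 107% and proportional error of 42.9%. Samples were taken at 48 and 50 h, then also at 168 and 170 h, then also at 336 and 338 h. CL/F was estimated by maximum a posteriori fit. Estimated and true dose-adjusted AUC were each regressed on a factor outside the prior, adjusting for Ccr, and the two coefficients were divided. Assumptions not in the article: 12-hourly dosing, Ccr between about 15 and 140 mL/min, and 2500-3000 virtual patients per scenario.

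| Samples used | Share of true coefficient recovered |
|---|---|
| Week 1 only | 29-36% (42% with the residual variance fixed at the population prediction) |
| One later pair only | about 40% |
| Two weeks pooled | 52-56% |
| Three weeks pooled | 62-67% (65-71% on the log scale) |

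Two further simulations of the same model gave 37%, 58% and 69%, and 38%, 64% and 70%, for 2, 4 and 6 samples.

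**5. In clinical units.** Take a factor that truly changes log CL/F by -0.366, a fall of 1 - e^(-0.366) = 31%. This size is an assumption. One simulation returned:

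- week 1: -0.136, or 37% of the truth, read as a 13% fall
- two weeks pooled: -0.212, or 58%, read as a 19% fall
- three weeks pooled: -0.251, or 69%, read as a 22% fall

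**6. Sensitivity.** The share is much the same if the factor acts through bioavailability (35% for week 1, 62-63% for three weeks). It is also similar if the true residual error is only 20% (34% and 63%), because the estimator still assumes 42.9%.

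**7. Factors correlated with Ccr.** With a correlation of 0.6, a single regression recovers 58% (week 1) to 78% (three weeks), since the part that runs through Ccr is not shrunk. The Ccr-adjusted coefficient is still only 35-68%.

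**The case against.** The strongest reply is that little depends on this analysis. It is one of many exploratory items, its P values are for reference only, and no dose, interim decision or end point uses its coefficients. The stated aim is to look for associations, and the protocol plans no step that adds a factor to the dosing model. All of that stands and limits the weight of the point.

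A reader might infer that shrinkage will hide real factors by making them non-significant. The documents do not support this. Uniform shrinkage scales the coefficient and its standard error together, so the P value does not change for that reason alone. In the week 1 simulation the partial correlation fell from 0.43 to 0.27, but mostly because the data are sparse and noisy, and no reanalysis of the same samples removes that.

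A reader might also infer that every candidate factor is equally affected. That is too broad. Age and weight enter Cockcroft-Gault, and the protocol plans single as well as multiple regressions. The full loss applies to Ccr-adjusted coefficients and to factors unrelated to Ccr.

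For modest effects, sampling error is larger than the bias. Take a 10% fall in clearance (an assumption; log -0.105). Recovery of 37-69% leaves a bias of 0.105 × 0.31 = 0.033 to 0.105 × 0.63 = 0.066. With 20 patients per group and clearance known exactly, the standard error is 0.272 × √(2/20) = 0.086. For the 31% fall the bias is 0.366 - 0.251 = 0.115 to 0.366 - 0.136 = 0.230, which exceeds it. So the bias dominates for large effects, which are the ones worth finding.

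Finally, pooling across weeks and reporting of shrinkage may well be settled in the full protocol or analysis plan, and their absence here is not held against the article. But the article does fix the outcome as an AUC built on post hoc clearance, and every pooling choice examined leaves a material bias.

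**Conclusion.** The point holds as a limited one about effect size. Ccr-adjusted coefficients for factors outside the prior, such as albumin or co-medication, will be about 30-40% of their true size if the outcome comes from week 1 samples, and about 50-70% if two or three weeks are pooled. Age and weight lose less in single regressions.

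This rests on the published model describing these patients adequately, on the estimator using the stated variances, and on Ccr being among the explanatory variables of the multiple regression. The range mainly reflects how many occasions feed the estimate, which the article leaves open. The primary end point and its test are untouched. The change is worth making because it is cheap and the planned coefficients cannot be read as effect sizes.

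**What to change.** In the Exploratory Analysis section, make the reported effect sizes those estimated on CL/F directly from all measured venous plasma concentrations in NONMEM. Fix the structural parameters of the published model or use them as priors, enter each candidate factor as a covariate on CL/F, and leave its coefficient free of any prior that would pull it to zero. Keep the regression on post hoc dose-adjusted AUC for screening only. State which occasions feed it and report the shrinkage of CL/F beside it. The Statistical Analysis section assigns all analyses to R, so add a line naming NONMEM for this one.

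The cost is some extra modelling in software the protocol already specifies (version 7.5.1). No new samples are needed: 40 patients with up to six concentrations each give at most 40 × 6 = 240 values. With 5 of 40 participants enrolled by 16 June 2025, there is time to specify it in advance. The change corrects the size of the estimates, not their precision. With 40 sparsely sampled patients the intervals will stay wide, and the results will also depend on how well the borrowed structural parameters fit this population.

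### The exploratory binomial test of pp65 clearance is set against a survey that, as reported, gives no clearance rate separate from toxicity

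*Protocol article*

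**What the plan says.** In the protocol article, Exploratory Analysis states: "The proportion of CMV antigen-positive cells that disappear in less than 3 weeks of treatment will be calculated", and then "a binomial test will be performed against the proportions in the preliminary study". No null value is given, and no toxicity condition is attached to the outcome.

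The survey is described only under Sample Size Calculation:

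- Size: "A preliminary survey was conducted among 20 patients admitted to the Department of Rheumatology and Clinical Immunology".
- Toxicity stops: "The proportion of patients who were unable to complete treatment with hematological toxicities was 65% (13/20").
- Other stops: "The proportion of patients who could not complete treatment for reasons other than adverse events was 5% (1/20").
- The remainder: "none of the other patients failed to become CMV pp65–negative within 3 weeks".
- The one success rate stated: "Approximately 30% of the patients achieved CMV pp65 negativity within 3 weeks without severe hematologic adverse events".

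Primary Analysis uses that same 30% as the null for the composite primary end point. Exploratory Analysis adds that its P values serve as references only.

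**The concern.** The outcome to be tested is clearance alone. The only success rate stated for the survey is for clearance without severe hematological events. These are different quantities: a survey patient who stopped for toxicity fails the composite, but may or may not have become pp65-negative by week 3.

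If 30% is used as the null, the survey's toxicity stops are read as virological failures, and ordinary clearance in the trial would look like a large benefit of TDM. If the rate among patients who did not stop early is used, the null is 100% and the test is degenerate. The choice between them decides the direction of the result.

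This is the only planned comparison of clearance alone with the survey. The composite can improve through less toxicity without clearance improving, so a reader will look to this comparison to separate the two.

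**Working it through.** **Inputs** (protocol article, Sample Size Calculation): 20 survey patients, 13 toxicity stops, 1 other stop, no failure to clear among the rest. Planned trial size: 40.

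**Step 1. Reproduce the stated figure.** 20 − 13 − 1 = 6 patients neither stopped early nor failed to clear. 6/20 = 30%, which matches the article. It is the composite rate.

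**Step 2. List the clearance rates the report allows.** The pp65 status of 13 + 1 = 14 patients is not given, so the rate among all 20 lies between 6/20 = 30% (none of the 14 cleared) and 20/20 = 100% (all cleared). Specific readings:

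- 6/20 = 30%: all 14 stops counted as not cleared.
- 6/7 = 85.7%: the 13 toxicity stops set aside, the other stop counted as not cleared.
- 19/20 = 95%: the 13 counted as cleared, the other stop as not cleared.
- 6/6 = 100%: all 14 set aside.

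**Step 3. Exact two-sided binomial test at n = 40, 5% level, for each null.**

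| Null | Significantly worse | Significantly better | P at 24/40 | P at 34/40 | P at 36/40 |
|---|---|---|---|---|---|
| 6/20 | 6 or fewer | 19 or more | 0.00009 (better) | 8e-13 (better) | 3e-15 (better) |
| 6/7 | 29 or fewer | 39 or more | 0.00006 (worse) | 0.82 | 0.65 |
| 19/20 | 35 or fewer | never | 3e-11 (worse) | 0.014 (worse) | 0.14 |
| 6/6 | 39 or fewer | never | 0 (worse) | 0 (worse) | 0 (worse) |

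Against 30%, 18/40 gives P = 0.056 and 19/40 gives P = 0.023. Against 100%, one failure gives P = 0, 40/40 gives P = 1, and superiority cannot be shown. So every result from 19/40 to 39/40 is better under one reported proportion and worse under the other.

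**Step 4. Cost of treating the survey rate as known.** The exact 95% CI is 11.9% to 54.3% for 6/20 and 54.1% to 100% for 6/6. Let trial and survey share the same true rate p, draw X from Bin(20, p) and Y from Bin(40, p), and test Y against the fixed null X/20. Summing the exact probabilities of P ≤ 0.05 gives:

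| True p in both | 0.3 | 0.5 | 0.7 | 0.9 |
|---|---|---|---|---|
| False-positive rate, one-sample binomial | 26% | 24% | 26% | 31% |
| False-positive rate, Fisher exact, 20 v 40 | 3.6% | 2.9% | 3.6% | 2.8% |

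So even a correctly extracted survey rate should not be used as a fixed null.

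**Step 5. The unit.** The sentence speaks of a proportion of cells. The survey counts patients, and Secondary End Points lists pp65 negativity within 3 weeks, a patient-level outcome. Patients are almost certainly meant.

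**The case against.** The strongest reply is that an article need not print every numerator and denominator for an exploratory test. The survey was done at the trial's own hospital, the charts may hold week-3 pp65 results for the 14 patients, and an analysis plan not shown here may state the rate. This stands in part. A reader might infer that no valid reference rate exists; the article shows only that none is reported. What remains is more than missing detail: the article commits to a one-sample test against survey proportions, the proportions it reports are mismatched or degenerate for that outcome, and the one-sample method ignores survey error whatever rate is used.

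A reader might also infer that the answer must be either far better or significantly worse. That overstates it. Against 6/7, results of 34/40 and 36/40 are neither, and the 100% null is one reading of the report, not a value the article states.

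A third tempting reading is that this is the trial's only check on antiviral effect. It is not. Weekly change in CMV antigen is a secondary end point, Secondary Analysis computes pp65 reductions and correlates them with AUC, and repositivity within 2 weeks of completion is collected. These are within-trial summaries, so the narrower statement holds: this is the only planned comparison of clearance alone with the survey.

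The reference to cells is loose wording and carries no weight of its own.

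**Conclusion.** The point holds in a limited form. As reported, the survey offers no clearance rate separate from toxicity; the possible values run from 30% to 100%, and the two that follow directly from the report give opposite conclusions for 19 to 39 cleared out of 40. Independently of that, a fixed null taken from 20 patients gives a false-positive rate of about 24% to 31% at equal true rates of 30% to 90%.

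These figures assume 40 evaluable patients, an exact two-sided test at 5%, and, for the false-positive rate, a survey rate based on all 20 patients.

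The consequence is confined to one exploratory analysis with reference-only P values. A reader might infer that the primary result is compromised; the documents do not support that, because the primary test has its own explicit 30% null, which matches its composite end point. The change is worth making, but the trial's main conclusion does not depend on it.

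**What to change.** 1. Define clearance per patient: pp65 negativity within 3 weeks of starting VGCV, whether or not treatment was completed. Write patients in place of cells, and state how a patient with no week-3 result is counted.
2. Extract the same outcome from the 20 survey charts and report its numerator and denominator.
3. Replace the one-sample binomial test with a two-sample comparison of trial and survey: the difference in proportions with a 95% CI, and Fisher exact test if a P value is wanted.
4. If the status of the 14 stopped patients cannot be recovered, drop the test and report the trial clearance proportion with an exact 95% CI. For example, 38/40 gives 83% to 99%.

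The cost is a change of wording and a look-up in 20 existing charts. The comparison will be less likely to look significant, which reflects the true precision of a 20-patient survey. With 5 participants enrolled as of June 16, 2025, the article's latest count, the earlier the definition is fixed, the fewer trial outcomes will be known when it is chosen.
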